### 2.2 Final statistical analysis plan

A summary of our final statistical analysis plan is included in the current manuscript, under the heading of “Statistical Analysis”. A detailed version of this is below.

For our primary outcome of whole-body lean mass at 12 months after intervention commencement, we calculated that a target sample size of 100 participants would provide a power of 90% at a two-sided alpha level of 5%, allowing for up to 20% attrition as seen in previously-published weight loss interventions. Notably, attrition at 12 months in our current trial was 16% (to be detailed in the Results section), which fell within the attrition prediction used in our sample size calculation. Specifically, to detect a 5% difference in whole-body lean mass (e.g. 50.3 kg versus 53.0 kg, and assuming a variance of 5 kg), the effect size is 0.52, so at 90% power and  $P < 0.05$ , a sample size of 39 participants per group would be necessary, therefore with 20% attrition we would need 50 participants in each group. Further, based on studies in participants with obesity that elicited comparable weight losses to that anticipated from the SEVERE intervention in this trial, i.e. 12-20% of initial body weight over 12 months, the effect size to detect differences between interventions in the change in bone mineral density are large ( $> 0.8$ ), indicating that a sample of 20 per group would provide 90% power to detect significant ( $P < 0.05$ ) differences between interventions.

Statistical analyses were performed using SPSS Statistics Version 24 for Windows (IBM Corporation, New York, NY, USA). Statistical significance was accepted as  $P < 0.05$ . Fisher's exact tests were used to compare categorical demographic characteristics (age, ethnicity) and attrition between groups (i.e. SEVERE versus MODERATE). To compare continuous variables between groups at baseline (0 months), Mann-Whitney tests were used. All continuous variables were assessed for normality before analysis using histograms and P-P-plots. Where data were not normally distributed, a natural log-transformation was applied to obtain a normal distribution, although means and confidence intervals are reported on untransformed data.

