As the degree of physical activity is known to influence measures of body composition, physical activity (expressed in metabolic equivalents of task, or METs) was added as a covariate, as measured at each of the timepoints. Maximum-likelihood estimation was used, and an unstructured covariance matrix was specified to account for the correlation between repeated measures over time by allowing the intercept for individuals to vary randomly. When the overall P value for the interaction between group and time was less than 0.05, Bonferroni adjustments were used to correct for multiple comparisons between groups at each time point. As a secondary analysis, the model was further adjusted for weight at each time point, because lighter individuals are known to have lower whole-body lean mass and BMD than heavier individuals. This was to determine if there was an effect of the interventions beyond that which would be expected due to weight loss.

Within-group changes were analysed with repeated measures linear mixed models. Intervention group and time were included in the model as fixed effects, and time as a repeated measure, with physical activity (METs) added as a covariate. Maximum-likelihood estimation was used, and an unstructured covariance matrix was specified. When the overall P value for the interaction between group and time was less than 0.05, Bonferroni adjustments were used to correct for multiple comparisons between time points and baseline (0 months) within each group.

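### The 12-month lean-mass contrast, powered as a single two-sided 5% test, has no test of its own and is described only behind an interaction gate with a Bonferroni correction of unstated size

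*Supplement*

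**What the plan says.** All of this is in the Supplement, section 2.2 (Final statistical analysis plan).

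- **Primary outcome.** The sample-size paragraph opens "For our primary outcome of whole-body lean mass at 12 months after intervention commencement", so there is one outcome at one time.
- **Design level.** The target of 100 participants "would provide a power of 90% at a two-sided alpha level of 5" per cent. No adjustment for multiple visits is mentioned.
- **Model.** One mixed model serves all outcomes. For lean mass, time has the levels 0, 4, 6 and 12 months, and the baseline value is also a covariate.
- **Comparison at a visit.** For an interaction P value below 0.05, "Bonferroni adjustments were used to correct for multiple comparisons between groups at each time point". The plan does not give the number of comparisons, exempt the 12-month contrast, or say what is concluded when the interaction is not significant.
- **Within-group change.** A second mixed model uses the same condition, a group-by-time interaction below 0.05. Bonferroni is then used to "correct for multiple comparisons between time points and baseline (0 months) within each group".

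Section 2.3 (summary of changes) explains the move from ANOVA/ANCOVA to mixed models but does not address this point.

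**The concern.** A single prespecified contrast at 5% already controls type I error for the primary question. It needs neither a prior omnibus test nor a share of alpha. The plan sizes the trial for that simple test, but the only visit-level comparison it describes is conditional and corrected. The primary conclusion may therefore be drawn at a stricter level than the trial was sized for, and the plan does not say how it is drawn if the interaction is not significant.

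For within-group change the problem is the kind of test. A group-by-time interaction asks whether the arms differ in their course. It does not ask whether either arm changed. If both diets caused the same loss of bone mineral density, the interaction would be null, and the plan describes no corrected visit-versus-baseline comparison for that case.

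**Working it through.** **1. The plan's own figure.** Inputs from section 2.2: "e.g. 50.3 kg versus 53.0 kg, and assuming a variance of 5 kg"; "the effect size is 0.52"; 90% power; two-sided 5%; "a sample size of 39 participants per group would be necessary"; "therefore with 20% attrition we would need 50 participants in each group".

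Two independent groups, normal formula: n per group = 2 × ((1.960 + 1.282)/0.52)² ≈ 78. The stated 39 does not reproduce. It does match the one-sample form, ((1.960 + 1.282)/0.52)² = 38.9. The attrition step holds: 39/0.8 = 49, and 50 × 0.8 = 40. The factor of two is a separate problem, and this point does not depend on it. What matters here is that 39 uses z = 1.960, one unadjusted two-sided 5% test. On that same formula a Bonferroni divisor would have given:

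- divisor 3: ((2.394 + 1.282)/0.52)² ≈ 50, or 63 per group after 20% attrition;
- divisor 4: ((2.498 + 1.282)/0.52)² ≈ 53, or 67 per group after attrition.

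**2. Cost of the correction alone.** Suppose the design really had 90% power at 5%. Then power at alpha/k = Φ(1.960 + 1.282 − z), with z the two-sided critical value at 0.05/k.

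| Comparisons | Alpha | z | Power (normal) | Power (t test, 42 per group) |
|---|---|---|---|---|
| 1 (as planned) | 0.05 | 1.960 | 90% | 90% |
| 3 (4, 6, 12 months) | 0.0167 | 2.394 | 80.2% | 79.6% |
| 4 (with time 0) | 0.0125 | 2.498 | 77.2% | 76.4% |

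The 42 per group is 50 × 0.84, from the reported 16% attrition, assumed even across arms. The divisors 3 and 4 are assumptions.

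**3. Cost with the gate.** Simulation: 40 per arm, 4,000 runs per row, visits at 0, 4, 6 and 12 months. All visits are equally correlated, at an assumed 0.8 or 0.9. The interaction was tested with Hotelling's T² with time 0 as a level, as the plan lists it. The 12-month contrast came from ANCOVA on baseline, with the effect set to give about 90% power at 5%.

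| Correlation | Effect | Gate opens | P<0.05, no gate | Gate and P<0.05 | Gate and P<0.0167 |
|---|---|---|---|---|---|
| 0.8 | constant at 4, 6, 12 | 88% | 89% | 82.5% | 74% |
| 0.8 | at 12 only | 88% | 89% | 83% | 75% |
| 0.9 | constant at 4, 6, 12 | 90% | 88% | 83% | 75% |
| 0.9 | at 12 only | 91% | 89% | 85% | 77% |

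With 42 per arm, a constant effect and a divisor of 4, gate plus correction gave 72–74%. Even if no alpha is lost to the correction, the gate alone takes 88–89% down to about 82.5–85%.

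**4. Within-group rule.** Let both arms change by the same amount δ at each visit. The between-arm difference in change is δ − δ = 0 whatever the size of δ, so the interaction is null and the gate opens in only about 5% of trials. This needs no assumption about the divisor.

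**The case against.** - **The divisor is unknown.** This stands. Baseline is compared separately by Mann-Whitney tests, so three comparisons are at least as plausible as four. Correction between the two groups within each visit would be a single comparison with no loss of alpha, though that leaves the phrase about multiple comparisons without content.
- **The text says when Bonferroni was applied, not that nothing is reported otherwise.** This stands as a reading of the words. It is still the only route to a visit contrast that the plan describes.
- **The gate might seem to block a sustained effect almost entirely.** A reader might infer this because a difference that is constant over 4, 6 and 12 months gives no interaction among those visits, and the gate would then open about 5% of the time. That needs a model without time 0. The plan lists time 0 as a level, so a constant later difference is an interaction, and the gate opened in 88–90% of runs.
- **A reader might blame this rule for all of the power shortfall at d = 0.52.** With 39 per group, two-sample power is already about 63% at 5%. That gap comes from the sample-size arithmetic, before any allowance for baseline adjustment, and should not be charged to this rule.
- **The rule is conservative.** This is correct. Bonferroni controls familywise error over visits, and that remains reasonable for 4 and 6 months.
- **Within-group change is not the randomised comparison.** True, and this makes it the lesser part. But the plan does set out a formal test for it, and its condition answers a different question.

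**Conclusion.** The point holds and should be fixed. The stated primary contrast has no dedicated test, and the described rule does not match the level at which the trial was sized. If the correction runs over visits, nominal 90% power becomes about 80% (divisor 3) or 76–77% (divisor 4). Adding the gate gives roughly 73–77% with divisor 3, and slightly less with divisor 4. If the correction runs only within a visit, the gate still costs some five points. These figures rest on assumed divisors, on visit correlations of 0.8–0.9 and on effect profiles that the documents do not give.

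The harm is lost power and an undefined decision when the interaction is not significant; type I error is not inflated. The within-group defect follows from the wording alone. The documents do not support the claim that the plan as written leaves a sustained between-group difference practically untestable.

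**What to change.** Replace the two conditional sentences in section 2.2 with wording such as:

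> The primary test is the group difference in whole-body lean mass at 12 months from the primary model, two-sided 5%, regardless of the interaction test and without Bonferroni correction. Differences at 4 and 6 months are secondary and corrected over those visits. Within-group mean changes with confidence intervals are reported at every post-baseline visit regardless of the interaction, corrected over those visits.

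For other outcomes, state the number of comparisons in the correction. If time 0 is ever taken out of the response, an interaction gate must not be kept, for the reason given under the objection.

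No new data are needed, only revised text and a re-run of existing contrasts. The change is not free, however. The final SAP is written in the past tense and already reports attrition at 12 months, so those data appear to have been seen. Label the change as post hoc, give the date, and report the gated, Bonferroni-corrected result beside the ungated one so that readers can see whether the conclusion depends on the choice.

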To compare longitudinal changes between groups, intention-to-treat analysis was performed using data from all participants originally randomized, using random effects linear mixed models. Mixed model analyses were used instead of standard repeated measures analysis of variance because of the likelihood that there would be dropouts and missed visits that preclude the use of the classical approach. Therefore, this model allowed for participants to have partial missing data and still be included without imputation. Intervention group and time (0, 4, 6, and 12 months for all parameters except for waist circumference, hip circumferences, and waist to hip ratio, which were assessed at all of these points plus at 0.25 and 1 months), were included as fixed effects, and participant was included as a random effect and included an intercept. Nominal

time was used, although measurements at 0 and 0.25 months were always done exactly 1 week apart, measurements at 1 month were done within  $\pm 2$  days from the exact date, measurements at 4 and 6 months were done within  $\pm 1$  week from the exact date, and measurements at 12 months were done within  $\pm 2$  weeks from the exact date. For all outcomes, baseline values of the relevant variable were added as a covariate in the analysis because when, by chance, there happens to be imbalance in the baseline covariate between groups, even when the two treatment groups are well balanced, adjusting for the covariates will (for linear models) give a more precise estimate of the treatment effect.

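### The 12-month lean-mass contrast was sized for one direct two-sided 5% test, but the final SAP reaches it only through a significant interaction and a Bonferroni correction whose divisor is not stated

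*Supplement*

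**What the plan says.** Section 2.2 (Final statistical analysis plan) opens its sample-size paragraph with one outcome at one time: "For our primary outcome of whole-body lean mass at 12 months after intervention commencement". It claims that 100 participants "would provide a power of 90% at a two-sided alpha level of 5" per cent, and makes no allowance for multiplicity.

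The between-group model in the same section is a linear mixed model with fixed effects for group and "time (0, 4, 6, and 12 months for all parameters except for waist circumference" and two related measures. Lean mass therefore has four time levels, three of them after baseline. The baseline value is also entered as a covariate for every outcome.

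Visit-level comparisons between groups appear in one sentence. "When the overall P value for the interaction between group and time was less than 0.05", the SAP says, "Bonferroni adjustments were used to correct for multiple comparisons between groups at each time point". Nothing in Sections 2.2 or 2.3 exempts the 12-month lean-mass contrast, specifies it as a direct test, or says what is concluded about it when the interaction is not significant.

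**The concern.** The test that was sized is not the test that is described. A single pre-named contrast needs neither an omnibus gate nor a correction for visits that are not primary. Under the written rule its significance level is below the stated 5%, its power is not the power calculated, and its status after a non-significant interaction is undefined.

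The direction matters. The original protocol (Part 2) asks whether the more severe diet causes lean-mass losses that may not be recovered. For a question of possible harm, an over-strict rule errs towards finding no difference.

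**Working it through.** **Inputs from Section 2.2.** Two-sided alpha 0.05; power 90%; "50.3 kg versus 53.0 kg, and assuming a variance of 5 kg"; "the effect size is 0.52"; 39 evaluable per group; visits at 0, 4, 6 and 12 months; baseline covariate. **Assumed, because not given:** the Bonferroni divisor k (3 post-baseline visits, or 4 if month 0 is counted) and the baseline-to-follow-up correlation r (0.5 to 0.9).

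**1. The plan's own figure.** For two groups, n per group = 2 × ((1.960 + 1.282)/0.52)² = 77.7, so 78. The stated 39 comes only from the one-sample form, ((1.960 + 1.282)/0.52)² = 38.9. This is a separate fault and is not counted below.

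**2. The plan's 90% on its own terms.** The one-sample form gives 0.52 × √39 = 3.247.
- alpha 0.05: Φ(3.247 − 1.960) = 90%
- 0.05/3 = 0.0167: Φ(3.247 − 2.394) = 80%
- 0.05/4 = 0.0125: Φ(3.247 − 2.498) = 77%

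So even if the sizing were right, the correction would remove 10 to 13 points.

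**3. Two arms of 39, baseline-adjusted, Bonferroni alone.** The noncentrality is 0.52 × √(39/2) / √(1 − r²) = 2.296/√(1 − r²). Power from the t distribution, approximately:

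| r | noncentrality | alpha 0.05 | 0.05/3 | 0.05/4 |
|---|---|---|---|---|
| 0.5 | 2.651 | 75% | 58% | 54% |
| 0.7 | 3.215 | 89% | 78% | 74% |
| 0.8 | 3.827 | 97% | 91% | 89% |
| 0.9 | 5.268 | >99% | >99% | >99% |

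**4. Adding the gate, with month 0 as a time level.** Simulation: 200,000 draws, large-sample Wald tests, 39 per arm, equal correlation r between all visits, 3-df interaction at 5%, then the baseline-adjusted 12-month test at 0.05/4. The comparator is the large-sample power for Bonferroni alone: Φ(2.651 − 2.498) = 56% at r = 0.5 and Φ(3.215 − 2.498) = 76% at r = 0.7. These run about two points above the t-based figures in step 3.

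| r | Bonferroni alone | gate, constant 0.52 from month 4 | gate, 0.52 at month 12 only | gate, fading 0.78, 0.65, 0.52 |
|---|---|---|---|---|
| 0.5 | 56% | 45% | 50% | 53% |
| 0.7 | 76% | 73% | 74% | 76% |
| 0.9 | >99% | >99% | >99% | >99% |

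The added cost is 3 to 11 points at r = 0.5, 0 to 3 points at r = 0.7 and nothing visible at r = 0.9.

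**5. No true effect.** The 12-month test alone would reject in 1.7% (k = 3) or 1.25% (k = 4). The gate lowers this to about 1%.

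**6. If month 0 is only a covariate.** The interaction then has 2 df and asks only whether the difference changes between 4, 6 and 12 months. For a constant difference its expected value is zero, so the gate opens at its own size, about 5%, whatever the size of the effect.

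**The case against.** **The divisor is inferred.** This is correct: 0.0167 and 0.0125 appear nowhere in the SAP. Where the authors mean a family of visits they say so, as in the within-group paragraph, which refers to comparisons of time points with baseline. Read literally, each visit has one between-group comparison and the correction does nothing. But the SAP then describes a correction for multiple comparisons where there is only one, and the gate remains. The family has to be stated on either reading.

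**The SAP does not forbid a direct test.** The conditional clause governs when Bonferroni is used, and silence is not a prohibition. A reader might infer that the primary contrast is barred after a non-significant interaction. The text supports only the weaker statement that no other route is given.

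**Baseline adjustment may leave ample power.** This stands in part. At r = 0.9 the loss is negligible when month 0 is a time level. A reader might instead quote the unadjusted t-test fall from 62% to 44% or 40%, but that ignores the baseline covariate in the SAP's own model. Nor is the gap between 90% and 62% caused by this rule; it comes from the sample-size arithmetic in step 1.

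**The rule is conservative, and confidence intervals are reported.** Type I error for this contrast is not inflated, and an estimate would probably still be visible. The declared decision would nevertheless not have the stated alpha or power.

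**Conclusion.** The mismatch holds on the text: one contrast is sized at two-sided 5%, and the only stated route to it is a significant interaction followed by an adjusted comparison. The rule errs towards missing a difference, with about 1% rejection under no effect.

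The power cost cannot be fixed at one number. For an effect of 0.52 with 39 per arm, Bonferroni alone costs about 17 to 21 points at r = 0.5, 11 to 15 at r = 0.7, 6 to 8 at r = 0.8 and almost none at r = 0.9. The gate adds up to 11 points at r = 0.5 and little from 0.7 upward. These figures assume a divisor of 3 or 4; the gate figures also assume equal correlations between visits and month 0 as a time level.

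A reader might infer that a persistent lean-mass deficit would almost never be declared, because the gate would open only about 5% of the time. That needs month 0 to be out of the response. The SAP lists month 0 as a time level as well as using baseline as a covariate, so the documents do not establish it. They do leave unclear what the interaction tests.

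**What to change.** Replace the gated rule for the primary outcome in Section 2.2 with wording to this effect:

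- The primary analysis is the SEVERE minus MODERATE difference in whole-body lean mass at 12 months, estimated from the mixed model with its 95% confidence interval and tested at two-sided 5% whatever the interaction P value.
- Differences at 4 and 6 months are secondary, with the multiplicity family and method stated.
- No between-group comparison is made at month 0.
- The interaction P value is descriptive.
- State whether month 0 is part of the response, a covariate, or both.

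The cost is SAP wording and one contrast from a model already fitted, with no new data or participants. Timing is the real constraint. Section 2.2 is written in the past tense and already reports 16% attrition at 12 months, so the change must be dated. If it was made after unblinded data were seen, label the direct contrast post hoc and report it beside the gated result. In that case a 5% type I error for the direct test cannot be guaranteed.

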### ***2.3 Summary of changes from original statistical analysis plan***

The final statistical analysis plan provides details that were not defined in our original statistical analysis plan.

Whereas our original statistical analysis plan included the use of repeated measures ANCOVA or ANOVA, our final statistical analysis plan used mixed models, in order to allow for missing data.

